**Fig. 1 Fig1:**
[figure not shown]
General overview of study design

**Table 1 Tab1:** Overview of conditions and intended N per condition

Name	Description of condition	N
RVE	Repeated vegetable exposure intervention: - exposure to either green beans or cauliflower as target vegetable during the first 19 days of weaning - five phone calls to motivate parents to expose children to vegetables at child age 4–6, 8, 13 and 16 months	60
VIPP-FI	VIPP-Feeding Infants: - exposure to fruits and a sweet vegetable (carrots) during the first 19 days of weaning - five home-visits using video-feedback to promote sensitive feeding at child age 4–6, 8, 13 and 16 months	60
COMBI	Combination of RVE and VIPP-FI	60
AC	Attention control group: - exposure to fruits and a sweet vegetable (carrots) during the first 19 days of weaning - five phone calls on development of child at age 4–6, 8, 13 and 16 months	60

*Note*. *RE* Repeated exposure, *VIPP-FI* VIPP-Feeding infants, *COMBI* Repeated exposure and VIPP-Feeding infants combined, *AC* Attention-control condition

Intervention effects are assessed both during and after conclusion of the interventions by performing a pre-test at the first two days of complementary feeding (child age 4–6 months; *t*_*0*_), two assessments during the interventions (at the end of the 19-day feeding schedule (child age 5–7 months; *t*_*1*_) and when the child is 12 months old (*t*_*12*_)), a post-test at the age of 18 months (*t*_*18*_) and two follow-ups when the child is 24 (*t*_*24*_) and 36 months old (*t*_*36*_). *T*_*0*_ and *t*_*1*_ are not scheduled at a standard, fixed child age but rather within a certain age range because we wanted to allow parents to start complementary feeding when they thought their child was ready. The other measurements *are* scheduled at set child ages because the intervention sessions following the very first start of complementary feeding are scheduled at fixed time points (see *Timing of intervention sessions* below). The timeline for participants is depicted in Table 2. Participants are allowed to stop at any point during the study if they no longer want to participate. If participants decide to withdraw from the study, discontinue an intervention or are unable to complete a specific assessment, they will be asked once whether they would still be willing to complete (parts of) the intervention, the post-test and/or follow-up assessments to come.

**Table 2 Tab2:** Timeline for participants

	Enrolment	Intervention-period						Post-test	Follow-up	
Child age (in months)	2–4	4–7		8	12	13	16	18	24	36
Time point		*t* _*0*_	*t* _*1*_		*t* _*12*_			*t* _*18*_	*t* _*24*_	*t* _*36*_
Enrolment & allocation										
1. Invitation e-mail	x									
2. Information and informed consent	x									
3. Screening	x									
4. Allocation	x									
5. Rice-flour porridge	x									
Interventions										
RVE										
Feeding schedule		days 1–19								
Phone-call		Twice in period days 3–17		x		x	x			
Provision of vegetable purees		X		x	x					
VIPP-FI										
Feeding schedule		days 1–19								
Home-visit		Twice in period days 3–17		x		x	x			
Provision of fruit and carrot purees		X		x	x					
Combined RVE + VIPP-FI										
Feeding schedule		days 1–19								
Phone-call + home-visit		Twice in period days 3–17		x		x	x			
Provision of vegetable purees		X		x	x					
Attention-control										
Feeding schedule		days 1–19								
Phone-call		Twice in period days 3–17		x		x	x			
Provision of fruit and carrot purees		X		x	x					
Assessment of study outcomes^a^		Days 1 + 2	Days 18 + 19		x			x	x	x

*Note.*
^a^Primary outcomes: vegetable intake and liking, child self-regulation of energy intake. Secondary outcomes: child anthropometrics, child eating behavior and maternal feeding behavior. RVE = repeated exposure to vegetables. VIPP-FI=Video-feedback Intervention to promote Positive Parenting-Feeding Infants

### Calculation of sample size

A power analysis was conducted to calculate the sample size necessary to detect a moderate effect size of .50, which is based on previous studies of the effects of repeated exposure to vegetables [27] and the effects of VIPP [72]. Given a power of .80 and an alpha of .05 the analysis showed that a sample size of 51 participants per group would be sufficient. Taking attrition into account, we aimed to include a total of 240 mothers, 60 per group (see Fig. 1 and Table 1).

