### Repeated exposure and sensitive feeding

Whether a combination of repeatedly exposing infants to vegetables and encouraging sensitive feeding may lead to a better vegetable intake and liking than each of the interventions alone, has never been tested before. However, there is evidence that presentation of beneficial food choices (succeeding at the *what*) in a non-responsive manner (failing at the *how*), and the presentation of unhealthy food choices (failing at the *what*) in a responsive manner (succeeding at the *how*) may lead to overweight and eating problems in children [43, 68]. For instance, an experimental study by Galloway and colleagues showed that pressuring a child to eat, even if this pressure is mild in nature, decreases the beneficial effects of repeated exposure to the taste of vegetables [43]. This suggests that an intervention aimed at both elements may be particularly powerful.

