### Aims and hypotheses

In summary, the *Baby’s First Bites (BFB)* study aims to test whether promoting the *what* and**/**or promoting the *how* of complementary feeding will result in increased vegetable consumption and liking and a better self-regulation of energy intake in infants and toddlers up until the age of 36 months. To this end, we will perform a superiority randomized controlled trial with parallel groups, comparing a) an intervention focusing on vegetable exposure (=what), b) an intervention focusing on sensitive feeding (=how), c) an intervention focusing on vegetable exposure and sensitive feeding (=what and how), and d) a control condition. The interventions will begin when the infant starts receiving complementary food (child age 4–6 months, as recommended by the Dutch Nutrition Center) and continue until the child is 16 months old. We hypothesize that a) all interventions are more effective in improving vegetable consumption and vegetable liking than the control condition without guidance on complementary feeding; b) the sensitive feeding and combined intervention will be more effective in supporting child self-regulation of energy intake than the vegetable exposure or control conditions; and c) the combined intervention is more effective than the other two interventions alone in promoting vegetable intake and vegetable liking. As the inclusion phase of the *BFB* study has already successfully been completed, the present article describes the characteristics of the sample of included participants as well as the design of this ongoing study.

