### Analyses

The intention-to-treat principle will be applied to all analyses. Whether the interventions differentially affect primary and secondary outcomes over time will be analyzed using linear mixed models analyses, a technique that makes use of every data point for every participant, irrespective of their missing data. The three intervention groups will be compared to the control group, and the combined group will be compared to the repeated exposure and the VIPP-FI group. A significance level of α = .05 will be used. The analyses will be corrected for relevant covariates such as family socioeconomic status, maternal consumption of vegetables, parental body mass index (BMI), child temperament, etc.

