## Discussion

*Baby’s First Bites* will be the first trial explicitly testing the separate and combined effects of promoting the *what* and *how* of complementary feeding. By comparing three prolonged, intensive interventions, we will be able to draw firm conclusions on what is most important to focus on when promoting vegetable acceptance and children’s self-regulation of energy intake in early childhood; what food to offer, how to offer this food, or a combination of the two. Moreover, this will be the first trial to include an intervention specifically manipulating sensitive feeding practices without manipulating any other variables, evaluating its effects using both self-report and observational measures. This allows conclusions on whether this parenting practice will indeed promote healthier food preferences in children and will foster children’s ability to self-regulate their energy intake, as is often suggested in the literature.

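### The stated power of .80 holds for one pairwise contrast of .50 tested one-sided; the protocol states it without that limit, while hypotheses (a) and (c) rest on five contrasts and an unsupported increment for the combined arm

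*Protocol article*

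**What the plan says.** Calculation of sample size (protocol article) gives one effect size, one power and one alpha. The calculation rests on "a moderate effect size of .50, which is based on previous studies of the effects of repeated exposure to vegetables [27". Studies of VIPP are named as the second source for this value. "Given a power of .80 and an alpha of .05", the result is 51 per group, raised to 60 per group (240 in total) for attrition. The section names no contrast and no sidedness.

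Aims and hypotheses sets out (a), that all three interventions improve vegetable consumption and liking more than control does, and (c), that "the combined intervention is more effective than the other two interventions alone in promoting vegetable intake and vegetable liking".

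Analyses plans three comparisons with control and adds that "the combined group will be compared to the repeated exposure and the VIPP-FI group". That makes five contrasts, with a significance level of .05.

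The Background section on repeated exposure and sensitive feeding says that whether the combination does better than "each of the interventions alone, has never been tested before". The Discussion says that "we will be able to draw firm conclusions on what is most important to focus on": what is offered, how it is offered, or both.

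**The concern.** A single power figure stands beside five contrasts, with nothing to say which of them it describes. The effect size comes from studies of each component alone. It therefore bears directly on a single intervention versus control, but on the combined arm (COMBI) versus a single arm only through an unstated assumption about how the two effects combine.

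The combination is the trial's novel question. A reader who carries .80 over to it could take a non-significant COMBI-versus-single difference as evidence that combining adds nothing, although a modest added effect would usually be missed. A reader could likewise take .80 as the chance of confirming hypothesis (a) in full.

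**Working it through.** **Inputs.** From Calculation of sample size: d = .50, power .80, alpha .05, 51 per group, 60 before attrition (51/60 = .85, so 15% implied). From Aims and hypotheses and Analyses: three contrasts with control, and COMBI versus repeated vegetable exposure (RVE) and versus VIPP-FI. Sidedness and the COMBI increment are not given, so both are shown as ranges.

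**Reproducing 51.** For two means, n per group = 2(z_alpha + z_power)²/d².
- One-sided: 2(1.645 + 0.842)²/.25 = 49.5. The t-test version gives 50.15, so 51; power at 51 is .806.
- Two-sided: 2(1.960 + 0.842)²/.25 = 62.8. The t-test version gives 63.8, so 64; power at 51 is .706 and at 60 is .775.
- A four-group ANOVA with f = .25 needs 178.4 in total, about 45 per group, which is not 51.

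So 51 is one pairwise comparison at d = .50, one-sided.

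**What one value of .50 implies across five contrasts.** If all three interventions are .50 above control, COMBI minus a single arm is .50 − .50 = 0. If the single arms are .50 above control and COMBI is .50 above each of them, COMBI is 1.00 above control. The second pattern is full additivity, which the protocol does not state.

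**Joint power.** Contrasts that share an arm have correlation .5, so joint power is not the product of the separate powers. It was simulated with four arms, normal outcomes, a pooled SD and no multiplicity adjustment.

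Hypothesis (a), all three interventions significantly above control, single arms at .50:

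| COMBI above control | 51 per group, one- / two-sided | 60 per group, one- / two-sided |
|---|---|---|
| .50 | .63 / .48 | .71 / .58 |
| .75 | .70 / .57 | .77 / .66 |
| 1.00 | .70 / .57 | .77 / .66 |

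Hypothesis (c), 51 per group, by assumed increment of COMBI over each single arm:

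| Increment | Each contrast, one- / two-sided | Both contrasts, one- / two-sided |
|---|---|---|
| .25 | .35 / .24 | .20 / .11 |
| .50 | .81 / .71 | .70 / .57 |
| .60 | .91 / .85 | .86 / .76 |

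At 60 per group, power for both contrasts is .23 / .14 at an increment of .25 and .77 / .66 at .50.

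**The case against.** A reader might infer that .80 has no application to hypotheses (a) and (c). The documents do not support that. The sample-size statement is conditional: a pairwise difference of .50 is detected with power .80. One-sided, this is true of any contrast of that size, including each arm versus control. It is also true of COMBI versus one single arm if the two cited effects add, because COMBI minus RVE is then the VIPP effect and COMBI minus VIPP-FI is the exposure effect.

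A reader might also infer that .80 is out of reach for (c) whatever the truth. It is not. The Background argues that the two components may reinforce each other, and an increment of .60 gives joint power .86 one-sided.

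Three further objections carry weight. No section makes the joint significance of several contrasts a criterion of success; that is a reading of how (a) and (c) are worded. The figure of 51 is the number left after attrition; with 60 per group the one-sided joint figures at full additivity fall only about 3 points short. The planned covariate-adjusted mixed models could raise power, although the sample-size section claims no such gain. Nor does the article say that a null combined-arm result would be read as no added benefit; that is a risk of misreading.

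What these objections leave untouched is that the limit to one contrast and the sidedness are unstated, and that the COMBI increment has no stated basis.

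**Conclusion.** The point holds as a limit on what the stated power covers. The number 51 is correct for a single contrast of .50 tested one-sided at .05, and two-sided it gives .71.

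For (a), read as all three interventions beating control, joint power is .63 to .70 one-sided (.48 to .57 two-sided) at 51 per group, and .71 to .77 (.58 to .66) at 60 per group with no attrition. These ranges assume single arms at .50 and COMBI at .50 to 1.00 above control.

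For (c), the answer depends on an increment that the article does not give. Over assumed increments of .25 to .60, joint power runs from .20 to .86 one-sided (.11 to .76 two-sided). An increment of .50 follows from the cited effects only under full additivity, and the article itself says the combination was untested. The Discussion's unqualified confidence on the combination is therefore not supported by the sample-size calculation. The joint figures rest on reading the hypotheses as worded, and the increments are illustrations.

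**What to change.** - **Calculation of sample size:** state that .80 is the power of a single pairwise contrast with a true difference of .50, and name the sidedness. Add the power of COMBI versus RVE and COMBI versus VIPP-FI over a range of assumed increments, marked as assumptions. If (a) and (c) are to be claimed as worded, add the joint figures.
- **Discussion:** limit the claim about the combination. Commit to reporting each COMBI-versus-single difference with a confidence interval, and say that a non-significant difference is not evidence that combining adds nothing.

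Recruitment is complete, so these are changes of wording that need no further families or data. The cost is a less favourable stated power and a more cautious claim on the combination.

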Third, we chose to deliver the combined intervention by simply following the same procedures as used in each separate intervention, and the intervention was provided by two different researchers/students (one delivering RVE, and one delivering VIPP-FI). As such, it can be debated whether this really constitutes a *combined* intervention or simply *two* interventions. Also, from the families’ point of view, receiving advice from two different persons might not be ideal. An alternative approach would have been to incorporate all information of both interventions in the home visits. However, we decided against this as the VIPP-FI home visits already took up 60 to 90 min. Including the information of the RVE intervention in this session would result in too much information for the mother to properly process in one sitting, increasing the risk that the effects of the intervention would diminish. Fourth, considering the time-consuming nature of this study for families, there will be a considerable risk of drop-out during the study. This risk is even higher in the selected sample of first-time mothers, as it is likely that many families will expand their family during the study period, making the time they have available for participating in this study more limited. We plan to accommodate families as much as possible to make sure that they will be able to finish the study, for instance by offering assistance where necessary (e.g., filling out questionnaires together or sending personal reminders) and by being flexible in planning the home-visits.

Finally, if the proposed RCT will prove the interventions effective, the labor intensiveness of the tested interventions may pose problems for their implementation to the general public. Although this is not so much a limitation of the current study, it is a drawback for implementing its results, as it will be necessary to translate the interventions to scalable prevention programs before the interventions can be implemented for a larger group.

In conclusion, the planned trial has the potential to provide valid evidence on the question how parents may promote healthy eating habits from the very first start of eating solid foods. If proven effective, these interventions could be useful to large scale effective prevention of childhood obesity.

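### The 51 per group matches an unstated one-sided 5% test; if the unqualified alpha of .05 is applied two-sided, power is about 71%, not 80%

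*Protocol article*

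**What the plan says.** The section Calculation of sample size sets out to "calculate the sample size necessary to detect a moderate effect size of .50". It continues "Given a power of .80 and an alpha of .05" and concludes that "a sample size of 51 participants per group would be sufficient". The recruitment target follows: "Taking attrition into account, we aimed to include a total of 240 mothers, 60 per group". No attrition rate is given; 51 out of 60 implies 1 − 51/60 = 15%.

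The Analyses section plans linear mixed models with covariates. It compares each intervention with control and adds that "the combined group will be compared to the repeated exposure and the VIPP-FI group". On the error rate it says "A significance level of α = .05 will be used".

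No section says whether the tests are one- or two-sided. The hypotheses under Aims and hypotheses are directional, for example that "all interventions are more effective in improving vegetable consumption and vegetable liking than the control condition", and the design is described as a superiority trial.

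**The concern.** A statistician who enters the three stated inputs into a standard two-sided calculation gets 64 per group, not 51. An alpha of .05 with no qualifier is normally taken as two-sided, and standard mixed-model output gives two-sided p-values. If the analysis is run that way, the design falls short of the power stated for it: the type II error for one unadjusted pairwise test at an effect of .50 is about 29% at 51 per group, not 20%. A non-significant contrast could then be over-read as evidence against a moderate effect.

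If one-sided testing was intended, a different problem arises. A one-sided 5% level is twice the one-sided 2.5% that a conventional two-sided test implies, and the article does not tell the reader that it is in use. Under either reading, the sample-size and analysis sections leave open a choice that decides whether 51 is enough.

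**Working it through.** **Inputs.** From Calculation of sample size: effect .50, read as a standardised mean difference d (the text does not spell this out); power .80; alpha .05; 51 per group, 60 after attrition; equal allocation. From Analyses: pairwise contrasts at alpha .05. Sidedness: not given.

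**Formulas.** Two independent means, normal approximation: n per group = 2(z_α + z_β)² / d², and power = Φ(d√(n/2) − z_α). Exact values use the noncentral t distribution.

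**Reproducing 51 (one-sided 5%).**
- Normal: 2(1.645 + 0.842)² / 0.25 = 49.5, so 50.
- Exact t: 50.15, so **51**, which matches the article.
- Exact power: 79.9% at 50 and 80.6% at 51.

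**Same inputs, two-sided 5%.**
- Normal: 2(1.960 + 0.842)² / 0.25 = 62.8, so 63.
- Exact t: 63.77, so **64**.
- At 51 per group: 0.5 × √25.5 = 2.525; Φ(2.525 − 1.960) = 71.4%; exact t 70.6%.
- At 60 per group: 0.5 × √30 = 2.739; Φ(2.739 − 1.960) = 78.2%; exact t 77.5%.

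| Per group | One-sided power (t) | Two-sided power (t) | d detectable with 80% power, two-sided |
|---|---|---|---|
| 51 | 80.6% | 70.6% | .56 |
| 60 | 85.9% | 77.5% | .52 |
| 64 | 87.9% | 80.1% | – |

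**Other routes to 51.** A four-group ANOVA with f = .25 needs 44.6, so 45 per group. With the largest difference between group means set at .50, the ANOVA needs 60 to 89 per group, depending on the pattern of means. None gives 51.

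**Covariate adjustment.** If a covariate has correlation ρ with the outcome, the residual variance is multiplied by (1 − ρ²). For 51 per group to reach 80% two-sided, 1 − ρ² = 51/63.77 = 0.80, so ρ is about .45. The article gives no correlation and does not say that the calculation used one.

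**The case against.** The strongest reply is that nothing in the article contradicts its own figure. Effect, power, alpha and n agree exactly under a one-sided test, no section says two-sided, and the hypotheses are directional. This stands, and it limits the finding. A reader might infer that the stated 80% is simply an arithmetic error. The article does not support that, because the 71% rests on the conventional reading of alpha and not on its text. Directional hypotheses do not settle the matter the other way, since they are common in superiority trials tested two-sided.

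A second reply is that a plain t-test is not the planned analysis. Mixed models with covariates may recover power: at 51 per group a correlation of about .45 would be enough, and at 60 per group a correlation of .3 would give about 81%. Both correlations are assumptions. The gain may be small where there is no like-for-like baseline: early intake is weighed puree, intake from 12 months comes from 24-hour recalls, and eating in the absence of hunger is first measured at 18 months. Even so, one cannot infer that every pairwise comparison is underpowered.

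Third, 255 families were randomised and 243 started, on average 255/4 = 63.75 and 243/4 = 60.75 per arm. Unadjusted two-sided power at those averages is about 80% and 78% before later losses. The 71% is thus the case in which arms shrink to the planned 51. The Discussion itself warns that "there will be a considerable risk of drop-out during the study", so some loss from these figures must be expected.

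**Conclusion.** The point holds in conditional form. Of the standard calculations tried on the stated inputs, only an unadjusted one-sided 5% comparison of two means gives 51 per group, and the article does not disclose that choice. If the tests are two-sided, 64 per group are needed for 80% power. Power is about 71% at 51 per group and about 78% with all 60 retained, with detectable effects of .56 and .52. These figures assume that .50 is a standardised mean difference, that allocation is equal, and that there is no gain from covariates or repeated measures.

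A reader might go further and infer that the hypothesis of the combined arm beating both single interventions contradicts the stated power, because two contrasts must succeed. The documents do not support this: the sample-size section claims no joint power, and the Analyses section lists the two contrasts without a rule that both must succeed.

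**What to change.** Before outcomes are analysed, state the sidedness of the tests in both Calculation of sample size and Analyses, so that the two agree.

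- **If two-sided:** replace the 80% with about 71% at 51 per group and about 78% at 60 per group, for an unadjusted pairwise comparison at an effect of .50. Give the detectable effects of .56 and .52. Add that covariate adjustment may raise the power by an amount that the article does not quantify.
- **If one-sided:** say that the calculation and all tests use a one-sided 5% level.

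Timing matters because a sidedness chosen after the results are known would not be credible. Inclusion is complete and no extra enrolment is needed. The change is one of wording; its cost is a less favourable stated power under the two-sided option, or open disclosure of a less strict error rate under the one-sided option.
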